**Fig. 1 Fig1:**
[figure not shown]
Schedule of enrolment, interventions, and assessments

Health and physical education teachers who deliver GoodForm will also provide feedback data for the project, should they consent to do so. HPE teachers will be recruited through direct contact or approached by their school principal, and will indicate their consent to run the program and complete lesson feedback using an electronic consent form, which will be returned to the research team. Principals will provide consent for the school to participate using an electronic consent form, however they will not be asked to provide any data for the study.

### Allocation and blinding

Participants will be allocated at the school level by a member of the research team using simple randomisation on a computer program with a 1:1 ratio (intervention:control). Neither the participants nor the researchers will be blind to the intervention condition.

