**Trial registration:**

This trial was retrospectively registered with the Australian and New Zealand Clinical Trials Registry on May 14th 2019, registration number ACTRN12619000725167.

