### Data analysis

The effectiveness of the intervention will be primarily determined through conduct of 16 generalized linear three-level mixed-effects regression models predicting our primary and secondary continuous outcome variables and two three-level logistic regression models predicting our primary categorical outcome variables. The effect of primary interest in these models is the fixed-effect of the intervention at the post-intervention and follow-up time points (i.e., the second and third time points, respectively). We will examine and account for potential clustering effects at both the school and classroom level. Missing data will be estimated using full-information maximum likelihood modelling. Within these models, we will additionally conduct mediation analyses to establish whether, and to what extent, the following variables mediate change in our dependent variables: internalisation – muscular, and internalisation – low body fat. Deviations from the above-described analysis plan will be fully described and justified.

To determine the required sample size for these analyses we conducted a comprehensive power analysis using RMASS (Roy, Bhaumik, Aryal, & Gibbons, 2007). We based our analysis on the following parameters; 3 measurement occasions (pre, post, followup), a conservative attrition rate of 5% from pre to post and 15% from post to 2 month follow up (which accounts for the longer time interval from post to followup), a small to medium effect size representing the hypothesized effectiveness of the intervention, equal numbers of students in the control and intervention arms, and a conventional alpha of .05. To achieve a power of .80, the analysis indicated that 504 students (252 in each of the intervention and control) were required. Thus, with a sample size of 600 the study is sufficiently powered with an appropriate amount of participants in case of natural attrition and unanticipated events that reduce participant numbers (e.g., student absence due to illness).

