### Protocol description and data availability

Protocol deviations, including sample size, program content, study populations, or other large modifications will be described in any publications resulting from the program. Data will not be available to the public, as participants are under 18 and we wish to maintain their total privacy as well as the privacy of the schools they attend. The final dataset will be accessible only to the research team.

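### All researchers are declared unblinded, with no exception for the analysis, while some modelling choices stay open; the analysis can be masked and its specification frozen first

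*Protocol article*

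**What the plan says.** Allocation and blinding says "Participants will be allocated at the school level by a member of the research team using simple randomisation on a computer program", and then "Neither the participants nor the researchers will be blind to the intervention condition". No role is excepted.

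Data management restricts the stored and downloaded data to the researchers, and Protocol description and data availability adds: "The final dataset will be accessible only to the research team". Intervention design describes how the same team combined and adapted two existing programs into Goodform. Background states a directional hypothesis in the program's favour.

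Data analysis plans "16 generalized linear three-level mixed-effects regression models" and "two three-level logistic regression models predicting our primary categorical outcome variables". On clustering it says "We will examine and account for potential clustering effects at both the school and classroom level". Its safeguard is "Deviations from the above-described analysis plan will be fully described and justified".

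**The concern.** In a teacher-delivered classroom program, boys and teachers must know what they receive, and all outcomes are self-reported. That route to bias cannot be closed by design. The analysis is different. Outcomes are self-completed electronically under unique codes, and arm is a single variable set by school, so the arm labels can be hidden from whoever fits the models.

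The article nevertheless fixes the opposite for every researcher. If a modelling choice is left until the data are in hand, it can then be made knowing which arm it helps, by people who built the program and expect it to work. What is at stake is the credibility of the between-arm comparisons, through a route that could have been closed cheaply.

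**Working it through.** **1. Number of models.** Outcome variables counted from Measures:

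- Male Body Attitudes Scale: 2 subscales
- Sociocultural Attitudes Towards Appearance Questionnaire: 7 subscales
- Outcome expectations and intentions for steroids: 2
- Social norms: 3
- Body talk: 2

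2 + 7 + 2 + 3 + 2 = 16 continuous. With the two yes/no use items, 16 + 2 = 18. This reproduces the count in Data analysis.

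**2. Who fits them.** The article names no analyst, so this step is an inference:

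- The researchers are not blind (Allocation and blinding).
- Only the researchers hold the data (Data management; Protocol description and data availability).
- Therefore whoever fits the models is one of the unblinded researchers.
- The research team developed the program (Intervention design).

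**3. What is fixed and what is open.**

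| Element | Status in the article |
|---|---|
| Scoring of the body image, sociocultural and attitude scales | Fixed: mean scores |
| Missing data | Fixed: full-information maximum likelihood |
| Model type for the two use items | Fixed: logistic |
| Effect of interest | Fixed: intervention effect at post-intervention and follow-up |
| Mediators | Fixed: muscular and low-body-fat internalisation |
| Cluster terms | Open |
| Family and link, 16 continuous models | Open: generalized linear, neither named |
| Outcomes for the mediation analysis | Open: three statements differ |

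**4. The open items in detail.**

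*Clustering.* The nested units are occasions, boys, classrooms and schools, which makes four, while the models have three levels. The text does not say which unit is left out or absorbed elsewhere, and it describes clustering as something to be examined. Schools are randomised, so whether and how the school term enters bears directly on the standard error of the intervention effect.

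*Mediation outcomes.* Sociocultural appearance attitudes names muscularity and body fat dissatisfaction: 2 outcomes. Study objectives and research questions names the primary outcomes: 2 body image + 2 attitude + 2 use = 6. Data analysis refers to the dependent variables in general. Read literally, that is up to 18, or 18 − 2 = 16 if the two mediators are not tested as outcomes.

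**5. Whether the reporting safeguard covers this.** The commitment to describe and justify deviations applies to departures from a stated plan. Choosing among readings that the plan leaves open is not a departure, so it need not be reported.

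**The case against.** **The blinding status is openly disclosed, and no researcher rates an outcome.** True, and nothing in the blinding statement is contradictory. That limits the weight of the point but does not answer it, because the remaining risk lies in the analysis, not in measurement.

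**Model details belong in an analysis plan that may exist.** This stands in part: an unseen plan could settle the cluster terms, family and link, and mediation outcomes. It does not dispose of the blinding statement, which is a positive and unqualified decision. An analysis plan that masked the analyst would conflict with it.

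**Masking would leak.** This also stands in part. The models need school and classroom identifiers, and a team that recruited the schools may recognise them by their sizes. Fixing the specification first still helps, because the choices are then made before any result by arm is seen.

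**Stronger readings that the documents do not support:**

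- *An inflated error rate caused by unblinding.* A reader might suppose that an arm-aware analyst takes the most favourable of k specifications whose test statistics correlate at r. The chance of a false result in the program's favour would then rise from 0.025 to 0.032 (k = 2, r = 0.95), 0.042 (k = 3, r = 0.90) or 0.057 (k = 4, r = 0.80). Neither k nor r is in the documents. Nor does the excess measure unblinding: an analyst masked to A/B who keeps the larger |z| has the same three rates in the program's favour, because with statistics this highly correlated the larger |z| almost always is the favourable one whenever a favourable one exceeds 1.96. By symmetry that analyst errs equally often against the program. A/B coding thus removes the one-sidedness, and only fixing the specification beforehand removes the inflation.
- *Registration and data access as aggravation.* A reader might add that "This trial was retrospectively registered" and that the dataset is closed to outsiders. Neither bears on whether the analyst is masked, and the article gives participants' age and privacy as its reason for restricting the data. Here the restriction serves only to identify who can analyse.
- *A wholly open analysis.* Most elements are fixed, as the table in the working shows.

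**Conclusion.** The point holds as a design choice that should be improved. The article declares all researchers unblinded, the analyst by inference is one of them, and three modelling choices can still be made with knowledge of the arms. This is a risk of bias, not evidence of it, and the documents give no basis for quantifying it. No sample size, power or alpha figure changes.

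The conclusion assumes that the blinding statement means what it says for every researcher, and that no separate document has already fixed the three open items. If one has, the remaining point is narrower: the blinding statement should still except the analysis.

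**What to change.** Amend Allocation and blinding to say that participants, teachers and the field team are not blind, but that the analysis is masked, in this order:

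1. Fix the cluster terms, the family and link for the 16 continuous models, and the mediation outcomes. Freeze the code on data without the arm variable, or with arm permuted, before outcomes are compared by arm.
2. Have an existing team member who does not analyse recode the arms as A/B. Remove school names and the fidelity data that exist only for the intervention arm.
3. Run the primary and secondary models on that file, and release the key when they are complete.

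Study objectives and research questions, Sociocultural appearance attitudes, and Data analysis should be brought into line on the mediation outcomes at the same time.

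Cost: a short protocol amendment and one recoding step. Fidelity summaries must wait until unmasking, and masking may be imperfect where school cluster sizes are recognisable.

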## Measures

All measures are self-report measures and were examined for suitability for adolescent males using the Simple Measure of Gobbledygook [40]. All measures were found to be suitable for a reading age of approximately 11 years and up. In total, boys’ questionnaires take approximately 15 min for each time point, with teacher questionnaires taking approximately 15 min in total.

### Body image

Two variables will assess the primary outcome construct of body image. These will be measured at all three time points. The Male Body Attitudes Scale [41, 42], a self-report measure that contains two subscales; muscularity dissatisfaction (7 items) and body fat dissatisfaction (5 items) will assess body image. Responses to items from both subscales are indicated on a 5-point Likert-type scale from 1 (*Never*) to 5 (*Always*), with higher scores indicating greater dissatisfaction. The mean score for each subscale will be used for analyses. Example items include “I think I have too little muscle on my body” (muscularity dissatisfaction subscale) and “I think my body should be leaner” (body fat dissatisfaction). Scores on the muscularity and body fat dissatisfaction subscales have demonstrated high internal consistency and construct reliability in young adult men [41], and have been validated in other body image research involving adult men [43, 44].

### Sociocultural appearance attitudes

The 28-item Sociocultural Attitudes Towards Appearance Questionnaire – 4 – Revised [45] will be used to assess appearance ideal internalisation and perceived pressure to achieve appearance ideals. Two subscales, internalisation thin/low body fat (two items, example item: “I think a lot about looking thin”) and internalisation muscular (four items, example item “It is important for me to look muscular”) will be used as secondary outcome measures and as mediators of change in muscularity and body fat dissatisfaction. The other subscales - pressures – media (five items, example item “I feel pressure from the media to look in better shape”), pressures – family (four items, example item “Family members encourage me to get in better shape”), pressures – friends (seven items, example item “My peers encourage me to increase the size or definition of my muscles”), internalisation – general attractiveness (two items that are reverse scored, example item “I don’t really think much about my appearance”), and pressures – general attractiveness (four items, example item “I feel pressure from my peers to improve my appearance”) will be used as secondary outcome measures. Responses to items for all subscales are indicated on a 5-point Likert-type scale from 1 (*Definitely Disagree*) to 5 (*Definitely Agree*) with higher scores indicating greater levels of internalisation or pressure. The mean score for each subscale will be used in analyses. Scores on all subscales of the SATAQ-4-R have good internal consistency in men [45] and have displayed good convergent validity (i.e., medium to large correlations) with other measures of body dissatisfaction and ED symptoms in men [46].

### Attitudes towards steroids

Outcome expectations for using steroids (OE-AAS; 4 items, [47]) and intentions to use steroids (I-AAS; 5 items, [47]) will be used to assess the primary outcome construct, attitudes towards APES, administered at all time points. Responses to both scales are indicated on a 7-point Likert-type scale, from 1 (*Strongly Agree*) to 7 (*Strongly Disagree*), with higher scores indicating less favourable attitudes towards steroids. The mean score for item responses from both subscales will be used in analyses. Scores for both scales have good to excellent internal consistency in men (α = .94 for OE-AAS and α = .92 for I-AAS) and evidence of good convergent validity, as demonstrated by correlations of .37–.44 with the Drive for Muscularity Scale [47].

### Use of supplements and steroids

Our final primary outcome is actual use of supplements and steroids, measured by two single items asking if participants have used either a) anabolic steroids within the past 3 months or b) supplements to build muscles or burn fat within the past 3 months. Responses to the items are indicated on a binary scale from 0 (*no*) to 1 (*yes*). Due to anticipated low baseline rates of use of supplements and steroids, statistical analyses are likely to be under-powered to detect reductions in use. However, frequency of use will be reported for this primary outcome variable.

### Social norms for using APES

Participants’ perceptions of social norms for using supplements and steroids (i.e., perceived prevalence, importance and acceptability of APES use among their peers) form three variables measuring the secondary outcome construct of social norms for APES. Items for these variables were adapted from Ling et al.’s [48] Peer Norms Scale of Physical Activity. Items concerning prevalence (example item: “How many of your close friends do you think take muscle building supplements?”) are measured on a 4-point scale, from 1 (*None*) to 4 (*All*), with higher scores indicating greater perceived prevalence of APES use. Items concerning importance (example item: “How important do you think it is to your close friends to avoid taking muscle building supplements?”) are measured on a 3-point scale, from 1 (*Not At All Important*) to 3 (*Very Important*), with higher scores indicating greater importance of avoiding APES. Items concerning acceptance (example item: “My friends would disapprove if they saw me using steroids.”) are measured on a 4-point scale, from 1 (*Disagree a lot*) to 4 (*Agree a lot*), with higher scores indicating less perceived acceptance of APES use. Scores on the Peer Norms Scale of Physical Activity, from which the scales in the present study were adapted have acceptable internal consistency α = .72, and acceptable one-week test-retest reliability of .78 [48].

### Negative body talk

Our final secondary outcome for boys will be negative body talk, the tendency to talk about concerns about fat and muscularity, assessed with the Male Body Talk Scale [49]. The scale comprises two subscales; muscle talk (6 items) and fat talk (10 items), and is measured on a scale from 1 (*Never*) to 7 (*Always*) with higher scores indicating more negative body talk. The subscales have excellent internal consistency in men (Muscle Talk α = .95, Fat Talk α = .92) and good evidence of convergent validity, with correlations between .20 and .58 on measures of body dissatisfaction and muscle dysmorphia [49].

### Teacher feedback

While not part of primary or secondary analyses, we will also examine teacher feedback scores for each topic within the program, using a scale adapted from McLean, Wertheim, Marques, and Paxton [50]. Four items for each topic measure level of student engagement, level of student understanding, the degree to which the activity was covered, and perceived activity success and items are rated from 1 (*not at all/low*), to 3 (*fully/high*). Optional qualitative feedback – specifically, any suggested changes for the lesson, and open-ended comments, may also be included.

### Data collection

All of the data for this study will be collected at the schools involved. Data collection will occur in the presence of the teacher facilitating the program. All teachers will be given instructions to conduct the survey in a quiet classroom, and to remind boys that they are free to refrain from answering any questions they do not want to. Boys will be instructed to complete their survey individually and to not look at others’ responses. Boys’ data will be collected using Qualtrics software, and teacher data will be collected using checklists in electronic (a Microsoft Word document) or paper form. Boys will be given a unique code so that their data can be matched over time and remain anonymous, with code lists stored separately from the data. Teachers’ data will only be identifiable to the research team. Upon completion of each stage of data collection, boys will receive information about how to seek support for any distress they may feel, including contact details for free and confidential support services and their school counsellor. Data collection forms can be requested from the research team.

### Data management

All student participant data will be entered electronically using Qualtrics software, and will be stored on password protected Qualtrics accounts accessible only to the researchers. Downloaded data will be stored on a password protected file accessible only to the researchers. All teacher data gathered either in paper format or electronically (a Microsoft Word document) will be transferred to a data sheet by the research team, and stored in a password protected file.

### Data analysis

The effectiveness of the intervention will be primarily determined through conduct of 16 generalized linear three-level mixed-effects regression models predicting our primary and secondary continuous outcome variables and two three-level logistic regression models predicting our primary categorical outcome variables. The effect of primary interest in these models is the fixed-effect of the intervention at the post-intervention and follow-up time points (i.e., the second and third time points, respectively). We will examine and account for potential clustering effects at both the school and classroom level. Missing data will be estimated using full-information maximum likelihood modelling. Within these models, we will additionally conduct mediation analyses to establish whether, and to what extent, the following variables mediate change in our dependent variables: internalisation – muscular, and internalisation – low body fat. Deviations from the above-described analysis plan will be fully described and justified.

To determine the required sample size for these analyses we conducted a comprehensive power analysis using RMASS (Roy, Bhaumik, Aryal, & Gibbons, 2007). We based our analysis on the following parameters; 3 measurement occasions (pre, post, followup), a conservative attrition rate of 5% from pre to post and 15% from post to 2 month follow up (which accounts for the longer time interval from post to followup), a small to medium effect size representing the hypothesized effectiveness of the intervention, equal numbers of students in the control and intervention arms, and a conventional alpha of .05. To achieve a power of .80, the analysis indicated that 504 students (252 in each of the intervention and control) were required. Thus, with a sample size of 600 the study is sufficiently powered with an appropriate amount of participants in case of natural attrition and unanticipated events that reduce participant numbers (e.g., student absence due to illness).

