## Methods

### Study design

We will use a cluster randomised-controlled trial to evaluate Goodform. Participants will be randomised at the school level to either the intervention or waitlist control condition. We will measure study outcomes at three time points: baseline, post-test, and follow-up (2 months post-test). Schools in the waitlist control condition will implement the program following completion of the follow-up questionnaire.

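### The article names maximum likelihood for school-randomised effects without giving the number of schools or a small-sample reference; if schools are few, restricted maximum likelihood with small-sample degrees of freedom is safer

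*Protocol article*

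**What the plan says.** Under Study design, the protocol article states: "Participants will be randomised at the school level to either the intervention or waitlist control condition". Under Data analysis it plans "16 generalized linear three-level mixed-effects regression models predicting our primary and secondary continuous outcome variables", plus two three-level logistic models for the binary use items. The effect of main interest is "the fixed-effect of the intervention at the post-intervention and follow-up time points". On clustering it says: "We will examine and account for potential clustering effects at both the school and classroom level". On estimation it says only: "Missing data will be estimated using full-information maximum likelihood modelling".

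The planned sample is 600 boys and alpha is 0.05. The article gives no number of schools, no intraclass correlation, no reference distribution for the tests and no degrees-of-freedom method. It does not rule out a small-sample method either.

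**The concern.** Full-information maximum likelihood is not a separate missing-data step in a mixed model. It means fitting the model by ML to all observed data, so the sentence in effect names the estimator for the intervention effects.

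That matters because the intervention varies only between schools. The information on its error variance comes from the number of schools, not from 600 boys. ML makes no allowance for the fixed effects when it estimates the between-school variance, so with few schools the standard error is too small. If the estimate is then referred to a normal distribution, a second source of optimism is added. At stake are the error rate and interval coverage of the intervention effects in the 16 continuous models. Kenward-Roger, a standard remedy, is built on restricted maximum likelihood (REML), so the named estimator does not fit it.

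**Working it through.** The article gives no type I error figure to reproduce. Its sample-size result (504 boys) does not bear on this point.

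**Inputs.** From the article: randomisation by school, 1:1; N = 600; alpha 0.05. Assumed: two-sided test; K schools of equal size, half per arm, K = 8 to 40; ICC 0 to 0.05; one time point; two levels (boys in schools); continuous outcome; no baseline adjustment.

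**Step 1: the bias in closed form.** The difference between arms has variance 4V/N, where V = (1 − ICC) + (600/K) × ICC is the expected between-school mean square. REML estimates V by SSB/(K − 2), where SSB is the between-school sum of squares. ML uses SSB/K. While the estimated school variance stays above zero, the ML standard error is √((K − 2)/K) times the REML one. The false-positive rate is then P(|t| on K − 2 df > c × √((K − 2)/K)), with c the critical value used.

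| K | √((K−2)/K) | 1.96 × ratio | Error, ML with z | t critical value × ratio | Error, ML with t on K−2 |
|---|---|---|---|---|---|
| 8 | 0.866 | 1.697 | 14.1% | 2.447 × 0.866 = 2.119 | 7.8% |
| 12 | 0.913 | 1.789 | 10.4% | 2.228 × 0.913 = 2.034 | 6.9% |
| 20 | 0.949 | 1.859 | 7.9% | 2.101 × 0.949 = 1.993 | 6.2% |
| 40 | 0.975 | 1.910 | 6.4% | 2.024 × 0.975 = 1.973 | 5.6% |

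These are limits, approached when the school variance is clearly above zero.

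**Step 2: simulation under the null.** At small ICCs the variance estimate is often truncated at zero, which lowers the error. With truncation and one million replicates per setting:

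| K | ICC | ML, z | ML, t on K−2 | REML, z | REML, t on K−2 |
|---|---|---|---|---|---|
| 8 | 0.01 | 9.5% | 4.1% | 7.3% | 2.9% |
| 8 | 0.03 | 12.9% | 6.7% | 9.2% | 4.4% |
| 8 | 0.05 | 13.6% | 7.4% | 9.5% | 4.8% |
| 12 | 0.01 | 7.6% | 4.5% | 6.2% | 3.6% |
| 12 | 0.03 | 9.7% | 6.3% | 7.5% | 4.7% |
| 12 | 0.05 | 10.3% | 6.8% | 7.8% | 4.9% |
| 20 | 0.01 | 6.3% | 4.7% | 5.5% | 4.0% |
| 20 | 0.03 | 7.6% | 5.8% | 6.4% | 4.8% |
| 20 | 0.05 | 7.8% | 6.1% | 6.5% | 4.9% |
| 30 | 0.01 | 5.6% | 4.6% | 5.1% | 4.2% |
| 30 | 0.05 | 6.8% | 5.8% | 6.0% | 5.0% |
| 40 | 0.01 | 5.4% | 4.7% | 5.0% | 4.3% |
| 40 | 0.05 | 6.4% | 5.6% | 5.7% | 5.0% |

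At ICC 0, ML with z gives about 4.5% at every K, so there is no inflation. A t test on the school-level mean square without truncation gives 5.0% throughout.

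**Step 3: which part does what.** At K = 8 and ICC 0.05, ML with z gives 13.6%. Correcting only the reference distribution brings it to 7.4%; correcting only the estimator brings it to 9.5%; correcting both gives 4.8%. The reference distribution is the larger contributor, but the named estimator contributes on its own.

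The t on K − 2 df stands in for Kenward-Roger or Satterthwaite, which were not simulated. Nor were the logistic models.

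**The case against.** The strongest reply is that the quoted sentence concerns missing data and names no test, reference distribution or degrees of freedom. Those are details that an article commonly leaves to the full protocol or analysis plan, and the larger part of the excess comes from a normal reference that the article never mentions. This stands as far as it goes: silence on degrees of freedom is not an error. What remains is that ML is named, that the section commits the team to justify departures from what it describes, and that ML leaves some excess even with a correct t reference when the ICC is 0.03 or more.

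Secondly, a reader might infer that no small-sample correction will be used and that error in all 16 models definitely exceeds 5%. The documents support neither. No correction is stated, but none is excluded, and the school count and ICC are unknown. At ICC 0.01 with t degrees of freedom, ML is not inflated at all (4.1% to 4.7% for 8 to 20 schools).

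Thirdly, the simulation is not the planned model. The plan has three time points, classroom as well as school clustering, and a comparison of change over time. If the tested contrast is a change, a stable school effect cancels, and the relevant quantity is between-school variation in change, which may differ from the ICCs assumed here. This stands as well: the percentages show the size of the risk under stated assumptions and are not this trial's error rate.

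**Conclusion.** The point holds conditionally. The article names an estimator that understates the error of a school-randomised effect when schools are few, and it gives no school count by which to judge whether that matters. For 8 to 20 schools, an assumed range for 600 boys, and an ICC of 0.01 to 0.05 for the tested contrast, ML with a normal reference gives roughly 6% to 14% false positives at nominal 5%. With t degrees of freedom and ML variance the figure is about 6% to 7% at ICC 0.03 to 0.05. With 30 to 40 schools, ML with a normal reference gives about 5% to 7% over the same ICCs. At ICC 0 there is no excess.

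This is an inexpensive improvement to a stated method, worth making before analysis. It is not a demonstration that the trial's tests are invalid.

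**What to change.** In the Data analysis section, or in the analysis plan with a note that it supersedes that sentence:

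- Fit the 16 continuous models by REML, with Kenward-Roger or Satterthwaite degrees of freedom for the intervention terms at post-intervention and follow-up.
- Allow school-level variation in the contrast actually tested. If the test is on change, include a school-by-time component; a school intercept alone is not enough.
- For the two logistic models, use between-within degrees of freedom or a school-level permutation test.
- State the number of schools.

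REML still uses every boy with any observed outcome, under the same missing-at-random assumption, so the purpose of the missing-data sentence is kept.

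**Cost.** It takes a software option and a sentence or two of text. Intervals become wider than under ML with z. With t on K − 2 df and the school variance clearly above zero, the factor is 2.101/1.859 = 1.13 at 20 schools and 2.447/1.697 = 1.44 at 8, with a matching loss of apparent power. If the ICC is near zero the test becomes conservative: with t on K − 2 df at ICC 0, rejection is 2.9% at 20 schools and 1.1% at 8. A permutation test is coarse with very few schools: with 8 split 4 and 4 there are 70 allocations, so the smallest two-sided p-value is 2/70 = 0.029. If schools turn out to be many, the change makes little difference.

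### The inputs listed for the 504-student, 80% power figure contain no clustering parameter, so the claim that 600 students is enough is unsupported for a school-randomised trial and probably optimistic

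*Protocol article*

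**What the plan says.** Under Study design, the protocol article states: "Participants will be randomised at the school level to either the intervention or waitlist control condition". The Background and the Allocation and blinding section say the same. The first paragraph of Data analysis plans three-level models that allow for clustering by school and by classroom.

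The second paragraph of Data analysis gives the sample size for those models. It lists its parameters: three occasions, attrition of 5% from baseline to post-test and 15% from post-test to follow-up, a type I error rate of 0.05, and "a small to medium effect size representing the hypothesized effectiveness of the intervention, equal numbers of students in the control and intervention arms". From these inputs it concludes: "To achieve a power of .80, the analysis indicated that 504 students (252 in each of the intervention and control) were required". The planned total is 600, of which the article says: "Thus, with a sample size of 600 the study is sufficiently powered". The same sentence explains the extra students by attrition and unforeseen absence.

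No section gives an ICC, a number of schools, a number of boys per school or class, or a design effect.

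**The concern.** Boys in one school tend to resemble one another, so 600 boys in a few schools carry less information than 600 independent boys. In a school-randomised trial, power depends mainly on the number of schools and the ICC. Every input the article lists describes students, and neither of these two quantities is among them.

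This goes beyond an article leaving detail to a longer document. It lists its parameters, derives a number and draws a conclusion of adequacy, so the claim has to stand on that list. Two things are at stake. A target of 600 students could be met with very few schools. And a null result could then be read as evidence of no effect from an adequately powered trial.

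**Working it through.** **Inputs from the document.** Power 0.80; alpha 0.05 (two-sided assumed, as sidedness is not stated); equal arms; retention at follow-up 0.95 × 0.85 = 0.8075; 504 required, 600 planned.

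**Inputs not in the document, assumed here.** Effect size d in SD units, ICC, boys per school m, number of schools k, and baseline–outcome correlation rho.

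**Step 1: the plan's own figure.** It cannot be strictly reproduced, because the effect is given only in words and no within-person correlation is stated. The plain two-sample formula for independent students is n per arm = 2(1.960 + 0.842)² / d². Total sample sizes are:

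| d | Total | Total if divided by 0.8075 |
|---|---|---|
| 0.20 | 786 | 974 |
| 0.25 | 504 | 626 |
| 0.30 | 350 | 434 |
| 0.35 | 258 | 320 |

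At d = 0.25 the formula gives 251.2, rounded up to 252 per arm, or 504 in total. That agrees with the printed figure only if the listed attrition and the repeated measures are ignored.

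**Step 2: could the margin to 600 absorb clustering?** 600/504 = 1.19. With design effect DE = 1 + (m − 1) × ICC, and none of the margin used for attrition, the largest ICC covered is 0.19/(m − 1). That is 0.008 at 25 boys per school, 0.004 at 50 and 0.002 at 100. The document assigns the margin to attrition and absence in any case.

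**Step 3: power with 600 students.** The setting is d = 0.25, one time point, equal clusters and no attrition. The standard error is √(4 × DE / 600), the noncentrality is 0.25 divided by that, and power comes from the noncentral t with k − 2 degrees of freedom. Baseline adjustment multiplies the variance by 1 − rho², with the same rho assumed at school level; rho = 0.6 gives 0.64.

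Example with 8 schools of 75 at ICC 0.02: DE = 1 + 74 × 0.02 = 2.48; effective N = 600/2.48 = 242; noncentrality = 0.25/√(4 × 2.48/600) = 1.94; power 37% on 6 degrees of freedom. With rho = 0.6 the noncentrality is 1.94/0.8 = 2.43 and power is 53%.

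| Schools × boys | ICC | DE | Power, unadjusted | Power, rho = 0.6 |
|---|---|---|---|---|
| 8 × 75 | 0.02 | 2.48 | 37% | 53% |
| 12 × 50 | 0.02 | 1.98 | 50% | 69% |
| 20 × 30 | 0.01 | 1.29 | 72% | 89% |
| 20 × 30 | 0.02 | 1.58 | 63% | 82% |
| 20 × 30 | 0.05 | 2.45 | 46% | 64% |

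**Step 4: sensitivity to d.** Without baseline adjustment, d = 0.35 at ICC 0.02 gives 62% with 8 schools and 90% with 20. With rho = 0.6, d = 0.30 at ICC 0.02 and 12 schools gives 84%.

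**The case against.** The strongest reply is that a loss of power has been assumed rather than shown. The effect size, ICC, number of schools and boys per school in the calculation are all outside the document. The planned models use baseline and two later occasions, which a single-time-point calculation ignores. The article says the power analysis was done for the three-level models, and an article condenses, so an unlisted clustering setting in the software cannot be excluded. All of this stands. Some scenarios do pass 80% once baseline is used.

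Two stronger readings are tempting and should be resisted.

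- A reader might take the agreement at d = 0.25 as proof that clustering was ignored. It is only a conjecture. With the stated attrition the same formula gives 626. Other routes also land near 504 after that attrition: d = 0.20 with baseline adjustment at rho 0.7 gives 498, and d = 0.25 on change scores at rho 0.6 gives 500. At d = 0.35 there would even be room for a design effect of 1.58 after attrition.
- A reader might set the students retained from 600 (600 × 0.8075 = 484.5, about 242 per arm) against 252 and call the trial short. Attrition is already listed as an input to the 504, so this counts it twice.

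The reply does not supply the missing basis. The text names its parameters, none describes clustering, and no other section does.

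**Conclusion.** The point holds in a limited form. The documented basis for 80% power contains nothing about clustering, so the statement that 600 students suffices is unsupported for a trial that randomises schools. It is probably optimistic, because the 1.19 margin would cover only a very small ICC even if attrition took none of it.

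That the trial lacks its stated power is not proven. In the five scenarios at d = 0.25 above, power runs from 37% to 72% without baseline adjustment and from 53% to 89% with an assumed correlation of 0.6. These figures take equal clusters, no attrition and no separate classroom effect. Unequal school sizes, attrition and classroom clustering would lower them; a larger true effect would raise them. The planned analysis does model clustering, so its validity is not in question here.

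**What to change.** Recompute the sample-size paragraph for the cluster design. State the numerical effect size, the number of schools, the boys per school, a range for the school and class ICC (for example 0.01 to 0.05), the assumed baseline–outcome correlation, and degrees of freedom based on schools. Say how attrition and the repeated measures enter. Replace the adequacy statement with the power range, or the minimum detectable effect, that 600 students in the actual number of schools delivers.

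The cost is recalculation and rewording; no extra enrolment is needed. The downside is that the stated power may become less favourable.
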